### Directly Observed Treatment (DOT)

DOT describes a system whereby patients taking a treatment dose are directly observed throughout the treatment course, thereby ensuring maximal compliance with the drug regime. In the context of malaria elimination, compliance is important for preventing the development of drug resistance and also fully removing the infectious reservoir from the population. To fully exploit the window of chemoprophylaxis, i.e. the period where drug levels protect treated individuals from being infected by an infectious mosquito bite, the entire target population needs to comply with the treatment regime. Therefore, a modified DOT schedule will be implemented wherein treatment is directly observed on day 1 and day 3, but not on day 2 for all individuals within a reactive response in the intervention and control arms. Treatment blister packs will be observed on Day 3 as a proxy of compliance for Day 2.

As stated in Section 2.2.2.1 on p17, DHAP needs to be taken on an empty stomach, and in certain cases this may prevent DOT being implemented.

## Surveys

The health centre catchment areas selected for this study will be enumerated fully prior to sampling for the end-line cross-sectional survey. Once randomization of health centers to each arm is complete, sampling buffers of at least 3km will be derived for each catchment in order to maintain an adequate distance between sampled households in differing study arms. The use of buffers for sampling is to prevent confounding of trial outcomes due largely to community level transmission effects crossing between study treatment groups. Such contamination could arise either due to the localized effects of the intervention on transmission geographically or due to mosquito movement between study areas. A second additional benefit of utilizing these sampling buffers will be to potentially reduce human cross-over between study areas. The sampling buffers will be derived based on geographic information system (GIS) layers mapping the health center catchment areas corresponding to areas administratively covered by a specific health center. These buffers will ensure that no households will be sampled within 3km of a study area which was randomized to a differing study arm. No sampling buffer will be applied where a catchment has been randomly allocated adjacent to another within the same treatment group, as in these situations there will be no difference in the intervention across the catchment boundary and no risk of cross-over/contamination between treatment groups.

Following complete enumeration of the study area, a simple random sample of households will be drawn from each catchment area as outlined in section 2.9 on p31, after restricting the sampling frame for sampling buffers in GIS. This process will be repeated for each survey time point.

A modified malaria indicator survey (Appendix 4) will be administered at the endline. The modified malaria indicator survey will include collection of the following information:

- Travel history
- Net ownership and use
- IRS history
- History of fever
- Treatment seeking behavior
- Household structure characteristics
- Household education
- Asset-based index to generate measures of wealth

The above information will be enable us to control for any differences between the selected health centre catchment areas.

All consenting individuals ≥ 1 month of age and < 15 years old in households participating in the surveys will be tested using an RDT and if positive given AL according to national treatment guidelines, or referred as appropriate e.g. if pregnant or suspected to be pregnant. Individuals will also be consented to provide finger prick blood samples (approximately 200 μL) collected as dried blood spots for:

- detection of asexual stage parasites by PCR
- serological responses to *P. falciparum* antigens
- serological responses to anopheline salivary peptides
- genotyping PCR positive samples using a molecular bar code

## Routine Data Reporting

Standard reporting of malaria incidence through passive cases presenting to community health workers and health clinics will be monitored and available for the study area and time period. This data is collected, aggregated - either weekly for Health Clinics or monthly for Health Posts, and then submitted by mobile phone. A complete list of data elements contained within the standard reporting is listed in Appendix 12.

## Consent

Written informed consent will be sought for each interaction. A summary of consent procedures is shown in Table 2. In the event that an individual refuses DHAP, the individual will be offered the standard of care in Zambia, which currently consists of RFTAT with an RDT and AL. To monitor refusal rates, the number of people who opt-out will be recorded.

Table 2 – Consent schedule and timing of data collection.

|  | Written informed consent for intervention | Written informed consent for DBS (finger stick) | Written informed consent for data collection |
| --- | --- | --- | --- |
| Endline Survey |  | X  (Appendix 3) | X  (Appendix 3) |
| Passive Case Detection |  |  |  |
| RFTAT intervention* |  |  |  |
| RFDA intervention | X  (Appendix 11) |  |  |
| Reactive Research Response (RFTAT / RFDA) | X  (Appendix 11 – RFDA Only) | X  (Appendix 8⁺) | X  (Appendix 8⁺) |
| - 3 day follow-up |  |  | X  (Appendix 8⁺) |
| - 30 day follow-up |  | X  (Appendix 8⁺) | X  (Appendix 8⁺) |
| - 90 day follow-up |  | X  (Appendix 8⁺) | X  (Appendix 8⁺) |

*Current routine strategy

⁺Individuals will be consented at the first visit for all subsequent interactions.

### Subject capacity

For individuals who do not have the capacity to provide consent for themselves, consent will be sought from the head of household or parent/guardian. If either is absent, the subject without capacity to provide individual consent will be excluded. If individuals are unable to sign consent forms, they may make a mark and a witness will attest to the subject’s consent.

## Research Strategy by Aim

### Primary Aim

Compare the effectiveness of RFDA using DHAP with RFTAT using AL in achieving zero seropositivity in children under 15 years of age.

Hypothesis: RFDA with DHAP will be more effective in reducing malaria prevalence in the community than RFTAT using AL by clearing parasites from RDT-negative individuals with subpatent parasitemia and through the longer chemoprophylactic protection conferred by DHAP.

**Design**: Cluster randomized controlled trial in which eight health center catchment areas are randomized to RFTAT with AL (control arm) and eight health center catchment areas are randomized to RFDA with DHAP (intervention arm)

**Population**: Residents (under fifteen years of age) of a random selection of households in health center catchments within the intervention and control arms using satellite imagery to define the sampling frame

**Outcomes**: 1) malaria seropositivity measured at endline;

**Inclusion/Exclusion criteria:** All consenting individuals aged ≥ 1 month and < 15 years will be tested for parasite prevalence in the survey

**Procedures**: 1) randomization; 2) RFTAT with AL or RFDA with DHAP; 3) endline survey

**Assays**: Serological analysis of DBS collected during endline survey

**Analysis**: For the outcome of seropositivity, a comparison of seropositivity will be made between intervention and control areas and between children stratified into younger (aged ≥ 1 month to < 2 years), middle (aged ≥ 2 years to < 5 years), and older (aged ≥ 5 years and < 15 years). To account for correlated data at the cluster level, mixed effects regression models with the health center as a random intercept will be the primary analytic method to estimate the effectiveness of RFDA compared to RFTAT for the outcome of malaria prevalence as measured through seropositivity. Analyses will account for environmental factors, socio-economic status, housing construction, education level, and demographic measures of the population as well ITN coverage and indoor residual spraying.

### Secondary Aim 1

Compare the effectiveness of RFDA using DHAP with RFTAT using AL in reducing RDT confirmed malaria incidence through passive case detection at health facilities

Hypothesis: RFDA with DHAP will be more effective in reducing malaria incidence in the community than RFTAT using AL by clearing parasites from RDT-negative individuals with subpatent parasitemia and through the longer chemoprophylactic protection conferred by DHAP.

**Design**: Cluster randomized controlled trial in which eight health center catchment areas are randomized to RFTAT with AL (control arm) and eight health center catchment areas are randomized to RFDA with DHAP (intervention arm)

**Population**: all residents of the health center catchment areas within the intervention and control arms presenting to a health facility with confirmed malaria by RDT or microscopy

**Outcomes**: 1) incidence of malaria confirmed by RDT or microscopy as measured through passive case detection at health posts and health centers

**Inclusion/Exclusion criteria:** Not applicable. Study will use aggregate health facility records of 16 health centers in the study.

**Procedures**: 1) RFTAT with AL or RFDA with DHAP; 2) routine passive case detection

**Assays**: None

**Analysis**: For the outcome of malaria incidence a Poisson or negative binomial regression with health center month as the unit of analysis will be generated. Total outpatient attendance will be used as an offset to account for treatment seeking behavior. Lagged environmental factors will be incorporated to account for seasonality of malaria transmission. Month of the year may be included to account for temporal autocorrelation.

### Secondary Aim 2

Compare the effectiveness of RFDA using DHAP with RFTAT using AL in reducing the prevalence of malaria and preventing re-infection in individuals receiving reactive responses.

Hypothesis: Among treated individuals, parasite clearance will be similar between those receiving RFTAT using AL and those receiving RFDA with DHAP. However, overall parasite prevalence following a reactive response will be lower in areas receiving RFDA with DHAP than in areas receiving RFTAT with AL because of clearance of subpatent infections and the longer protective effect of DHAP.

**Design**: longitudinal cohort study

**Population**: residents within the intervention and control arms receiving a reactive research response

**Outcomes**: 1) PCR parasite prevalence at 0, 30 and 90 days following a reactive research response

**Inclusion/Exclusion criteria:** All consenting individuals aged ≥ 1 month will be tested for parasite prevalence 0, 30 and 90 days following the reactive research response. Individuals to be included in the assessment of secondary aim 2 will have parasite measurements at 0, 30 and 90 days following the reactive research response.

**Procedures**: 1) reactive response; 2) follow-up visit at 30 days; 3) follow-up visit at 90 days

**Assays**: PCR for asexual parasites using DBS collected at 0, 30 and 90 days

**Analysis**: Parasite prevalence at 30 days and 90 days will be analyzed separately. Areas receiving a reaction will form the unit of analysis while malaria infections during returns to the areas receiving a reaction will be measured as a count variable. A mixed effects Poisson regression with the offset being the number of individuals providing filter paper with a DBS during the return to the areas receiving a reaction will be used to compare the effectiveness of RFDA v. RFTAT at clearing an area of malaria infections (30 days) and preventing reintroduction following the reactive response (90 days). A number of factors will be tested for acting as effect modifiers through a test for interaction including initial parasite prevalence at day 0 during the response, response coverage in the area, asset-based wealth index, vector control coverage of the area, age and demographics of the individuals living in the area, as well as environmental factors such as vegetation cover and topographical measures. A fixed effects regression approach, wherein the difference between the number of malaria-infected individuals at day 0 during the reaction and the number of malaria-infected individuals at day 30 and/or day 90 following the reaction may be used to assess how the malaria parasite reservoir changes following the reactive responses.

### Secondary Aim 3

Compare the cost-effectiveness of RFDA using DHAP with RFTAT using AL in reducing the prevalence of malaria in the community.

Hypothesis: RFDA will be more cost-effective in reducing malaria prevalence than RFTAT by clearing parasites from individuals with subpatent parasitemia, through the longer protective effect conferred by DHAP, and the cost savings of not using a diagnostic test (RDT).

**Design**: cluster randomized trial

**Population**: all residents of the health center catchment areas within the intervention and control arms

**Outcomes**: Costs associated with RFTAT and RFDA, including personnel, transportation, and commodities.

**Inclusion/Exclusion criteria:** Not applicable. Study will use cost estimates and estimates of reduction in parasite prevalence as measured in Primary Aim.

**Procedures**: 1) randomization; 2) RFTAT with AL or RFDA with DHAP; 3) follow-up visit on day 3 to assess adverse reactions; 4) measurement of costs

**Analysis**: Detailed tracking of program expenditures on the establishment, production and delivery components of the RFDA and RFTAT interventions, including the value of time spent by the CHWs and other staff, will be used to calculate the financial costs. Costs will be calculated using an ingredients approach that involves enumerating both the quantity of specific inputs (e.g., hours spent, number of rapid diagnostic tests used, etc.) and the time spent during the intervention. As the analysis is intended to be incremental, existing infrastructure and recurrent inputs that would be present in the absence of the intervention will not be costed. The emphasis of the cost analysis is on determining the cost of RFDA and RFTAT alone, and not assessing the cost of training CHWs in the diagnosis and treatment of malaria nor in the follow-up visits to areas receiving reactive responses. Cost-effectiveness will then be measured through incident malaria cases averted as measured through the difference in malaria incidence at health centers in RFDA and RFTAT arms.

### Secondary Aim 4

Measure the proportion of *P. falciparum* infections likely attributable to importation and local transmission using parasite genotyping as well as defining genotypes spatial distribution.

Hypothesis: The proportion of *P. falciparum* infections attributable to importation will increase in both the intervention and control arms as local transmission is interrupted through the reactive case detection strategies. Additionally, the genetic diversity of locally transmitted parasites will decrease as transmission decreases but will be lower in communities receiving RFDA.

**Design**: nested cross-sectional study

**Population**: All individuals with a positive RDT for *P. falciparum* identified in the endline survey and during reactive case detection and their evaluation in reactive research responses.

**Outcomes**: Parasite population genetics, and spatial distribution of defined parasite genotypes.

**Inclusion/Exclusion criteria:** All individuals tested for malaria during the endline survey as well as during reactive research responses who have consented to further analyses of their dried blood spot sample.

**Procedures**: Sample collection from 1) reactive responses; 2) endline survey; genotyping of PCR-positive samples

**Assays**: Genotyping of *P. falciparum* genomes using PCR-positive DBS

**Analysis**: All malaria infections will be geo-referenced through data collection. Spatial variation in the genomic complexity and diversity will be estimated using the Geneland

^34^package in R

^35^ which uses Bayesian methodology to identify clusters of individuals with similar genotypes while accounting for spatial dependence of geo-referenced data. The procedure is capable of analyzing multivariate gene outcomes including SNPs. The number of separate genetic populations in the study area will be estimated and mapped; migrants (*P. falciparum* infections dissimilar genetically from others in nearby space) will be classified as imported malaria cases without onward transmission and will also be identified and mapped. The influence of a number of environmental factors on the spatial distribution of malaria parasites will be estimated. The enhanced vegetation index available through remotely sensed data will provide an indicator of adult mosquito habitat

^36,37^. A digital elevation model will be used provide an indicator for the propensity of an area to harbor mosquito breeding sites

^38–40^. We aim to utilise spatio-genetic methods that have been utilized in various aspects of ecology, but have not yet been applied to malaria epidemiology to understand transmission dynamics in the two arms

^41^.

Genetic complexity, defined as the number of genetically unique parasites found within health centre and health post catchments, will be compared between RFDA and RFTAT areas using a Poisson or linear regression depending upon the number of genetically unique parasites found. A number of factors will be tested including proximity of the area to the main road, wealth of the area, vector control coverage of the area, age and demographics of the individuals living in the area, as well as environmental factors such as vegetation cover and topographical measures.

### Secondary Aim 5

Assess the utility of serology to measure short-term changes in malaria transmission and evaluate malaria elimination programs

Hypothesis: Different serological outcomes will be both time sensitive and more prevalent than detected malaria parasite infections leading to less costly evaluation of malaria elimination programs

**Design**: nested longitudinal study

**Population**: all residents enrolled for a reactive research response within the intervention and control arms

**Outcome measures**: Antibody responses to appropriate *P. falciparum* antigens, e.g. AMA1 and MSP_1-19_.

**Inclusion/Exclusion criteria:** All individuals tested for malaria during the endline survey as well as during reactive research responses who have consented to further analyses of their dried blood spot sample.

**Procedures**: 1) randomization; 2) endline survey; 3) measurement of antibodies to *P. falciparum* antigens

**Assays**: Enzyme immunoassay to measure IgG antibodies to *P. falciparum* antigens from DBS

**Analysis**: The correlation between malaria parasite prevalence and various estimates of serology will be assessed in the endline survey samples. The analyses listed in the primary aim assessing the effectiveness of the intervention to reduce malaria parasite prevalence and malaria incidence will be repeated with the outcomes of serology and effect estimates will be compared.

The spatial variation of malaria parasite prevalence will be compared with the spatial variation of individuals measuring exposure to *Anopheles* spp. antigens (see below).

### Secondary Aim 6

Assess the feasibility of using remotely sensed malaria risk maps to identify areas with higher potential for local malaria transmission

Hypothesis: Exposure to anopheline mosquito salivary peptides as measured by serology will be correlated with the spatial distribution of malaria parasite infections and can be predicted through mapping mosquito habitat

**Design**: nested case-control study

**Population**: all residents of reactive research responses within the intervention and control arms. Cases will be defined as individuals testing positive for malaria during a reactive research response. Controls will be defined as individuals testing negative for malaria during a reactive research response.

**Inclusion/Exclusion criteria:** All individuals tested for malaria during reactive research responses.

**Outcome measures**: Antibodies to anopheline salivary peptides

**Procedures**: 1) randomization; 2) endline survey; 3) measurement of antibodies to anopheline salivary peptides

**Assays**: Enzyme immunoassay to measure IgG antibodies to anopheline salivary peptides using DBS

**Analysis**: The association between the spatial location of a household of an individual having a malaria infection and the spatial location of individuals being exposed to anopheles mosquitoes as measured through serological reaction to anopheline salivary peptides will be measured using an odds ratio. Three risk surfaces will be generated using kernel intensity functions. First, a simple risk surface of malaria infections compared to non-infected individuals will be generated using an adaptive bandwidth

^42^. Second, a simple risk surface of exposure to anopheline salivary peptides compared to unexposed individuals will be generated using an adaptive bandwidth

^42^. Third, a more complex risk surface will be modeled from remotely sensed *Anopheles* breeding sites based on topographical indices derived from remotely sensed digital elevation models

^38–40^. This more complex risk surface will utilize a kernel intensity function with a fixed bandwidth representing mosquito dispersal based on ongoing literature review of mark-release-recapture studies. The similarity between risk surfaces will be measured through estimating the correlation of pixel values at the location of each individual. We will compare the geographic footprint of clusters of malaria infection and proximity to remotely sensed *Anopheles* breeding sites.

### Secondary Aim 7

Assess the utility of a HS RDT in identifying additional standard RDT sub-patent infections in the RFDA arm

Hypothesis: Reducing the limit of detection will enable additional sub-patent infections to be identified

**Design**: nested cross-sectional study

**Population**: Residents within the control (RFDA) arm receiving a reactive research response

**Inclusion/Exclusion criteria:** All consenting individuals enrolled during reactive research responses in the RFDA arm

**Outcome measures**: Incidence of malaria from standard RDT, HS RDT, *Pf* HRP2 Quansys Q-plex ELISA (Logan, Utah; Q-plex ELISA) and PCR

**Procedures**: 1) reactive response in RFDA arm

**Assays**: HS RDT and standard RDT on consenting individuals in the field, PCR (including *Pf* HRP2/3 gene deletions) and Q-plex ELISA on DBS

**Analysis**: The HS RDT performance will be measured by sensitivity, specificity, negative and positive predictive values (NPV, PPV) against RDT, PCR, and Q-plex ELISA results. The data from all assays / tests will be used in descriptive analyses including the distribution of parasitemia (PCR), HRP2 (Q-plex ELISA), *Pf* HRP2 detection by RDT and HS RDT, and if present, the prevalence of *Pf* HRP2/3 deletions.

Although abundant during infection, the half-life of HRP2 is long and can remain present despite parasite clearance by treatment; as a result, there is a need to define false positives by PCR and also by an independent *Pf* HRP2-based assay. The Q-plex ELISA contains spots for *Pf* HRP2 and Pan-malaria LDH. The capture and detection antibodies are orthologous to those on the RDTs and therefore confirm the presence or absence of *Pf* antigenemia. The Q-plex ELISA also quantifies both *Pf* HRP2 and Pan-LDH. The *Pf* HRP2 measurement, as well as the standard PCR detection results, will be used to further define the limit of detection of *Pf* HRP2 and parasitemia respectively by the HS RDT in an endemic area. Additionally, for DBS specimens that are positive for *Pf* by qPCR, but negative by all *Pf* HRP2-based tests/assays (RDT, HS RDT, and Q-plex ELISA), a *Pf* HRP2 and *Pf* HRP3 (HRP2/3) deletion PCR will be performed.

### Secondary Aim 8

We will determine the direct and spillover effects of the RFTAT / RFDA interventions and assess whether effects vary by intervention coverage, distance to intervention, and time from incident case detection. We will then pool the data with two other similar studies from Namibia and Swaziland and perform a meta –analysis of the outcomes.

Hypothesis: Reactive case detection impact is not limited to the radius of the intervention, but is anticipated to be weak therefore data needs to be pooled to increase the power and maximize the likelihood of identifying spillover effects.

**Design**: longitudinal cohort study, primary health facility incidence data

**Population**: all residents within the study area

**Outcomes**: 1) PCR parasite prevalence at 0, 30 and 90 days following a reactive research response, 2) health facility incidence data

**Inclusion/Exclusion criteria:** All consenting individuals aged ≥ 1 month will be tested for parasite prevalence 0, 30 and 90 days following the reactive research response.

**Procedures**: 1) reactive response; 2) follow-up visit at 30 days; 3) follow-up visit at 90 days 4) health facility reported incidence data

**Assays**: PCR for asexual parasites using DBS collected at 0, 30 and 90 days

**Analysis**: We will estimate direct effects and spillover effects of reactive, focal malaria elimination interventions on Plasmodium falciparum malaria incidence and prevalence and assess whether effects vary by intervention coverage, distance to intervention, and time from incident case detection. The direct effects analysis will include individuals/ households that received interventions, and the spillover effects analysis will include those who did not receive interventions but are in the study area. Parameters will compare outcomes in each group between arms overall and conditioning on intervention coverage, distance to intervention, and time from incident case detection. We will perform an individual participant meta-analysis. First we will estimate effects in each of three cluster-randomized trials; then we will pool effects using fixed and random effects.

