# Research Plan

## Study Design

The study design will be a cluster randomized trial comparing an enhanced strategy for malaria elimination (RFDA with DHAP) with the current strategy (RFTAT with AL). Impact evaluation will consist of: 1) community-based, cross-sectional measurement of malaria seropositivity in children aged ≥ 1 month and < 15 years through a random sample survey at the end (two years) of the intervention period; 2) longitudinal follow-up of a subset of individuals participating in reactive responses by a research team; and 3) detection of incident malaria cases and total outpatient attendance at health centers and health posts.

A total of sixteen health centers will be targeted in this RCT (Table 1). The proposed areas were selected from the 11 districts within Southern Province, Zambia that have successfully implemented RFTAT surveillance with the following criteria: a mean monthly incident malaria case load of < 25 and a mean test positivity during ongoing RFTAT of at least 5%. Where multiple health centers fulfilled the inclusion criteria, preference was given to those that are geographically close to one another (minimum 5km buffer to reduce contamination) and are accessible all year round. Selected health centres will be randomized to either control or intervention arms, with 8 health centers per arm (Figure 3).

| Organisation Unit | Confirmed Cases of Malaria (Sep ’13 – Aug ’14) | | | | Positivity Rate (%) during RFTAT |
| --- | --- | --- | --- | --- | --- |
|  | Clinic | Community | Total | Average cases per month |  |
| Chisekesi Rural Health Centre | 176 | 77 | 253 | 21 | 9.4 |
| Habulile Rural Health Centre | 133 | 109 | 242 | 20 | 9.3 |
| Katombora Health Post | 123 | 78 | 201 | 17 | 12 |
| Kazungula Health Post | 71 | 20 | 91 | 8 | 7.9 |
| Keemba Rural Health Centre | 58 | 89 | 147 | 12 | 6.8 |
| Mayoba Rural Health Centre | 46 | 37 | 83 | 7 | 9.4 |
| Moonde Rural Health Clinic | 0 | 214 | 214 | 18 | 8.3 |
| Mubanga Rural Health Centre | 77 | 139 | 216 | 18 | 5.3 |
| Mukwela Rural Health Centre | 86 | 157 | 243 | 20 | 7.8 |
| Munkolo Rural Health Centre | 42 | 76 | 118 | 10 | 6.9 |
| Musokotwane Health Post | 38 | 53 | 91 | 8 | 8.2 |
| Muzya Rural Health Centre | 40 | 83 | 123 | 10 | 9.9 |
| Nadezwe Rural Health Centre | 58 | 107 | 165 | 14 | 11.2 |
| Namwianga Urban Health Centre | 56 | 140 | 196 | 16 | 5.2 |
| Ngwezi Rural Health Centre | 11 | 169 | 180 | 15 | 8.3 |

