| Pangwe Rural Health Centre | 21 | 127 | 148 | 12 | 19.2 |
| Siachitema Rural Health Centre | 14 | 119 | 133 | 11 | 7.4 |
| Simooya Rural Health Centre | 142 | 40 | 182 | 15 | 8.7 |
| Zambia National Service Rural Health Centre | 78 | 40 | 118 | 10 | 10.7 |
| ZCA Rural Health Centre | 215 | 47 | 262 | 22 | 8.3 |

Table 1 – Proposed selected health centre catchment areas along with data from these facilities for the last year.

**Control Arm** - PCD at health centers and health posts, with RFTAT in response to RDT confirmed incident malaria cases as currently outlined in the Step D protocol (Appendix 1). RFTAT consists of screening all individuals within 140 meters of an incident malaria case using a RDT and treating those testing positive with AL.

**Intervention Arm** - PCD at health centers and health posts, with RFDA in response to RDT confirmed incident malaria cases. RFDA consists of treating all individuals within 140 meters of an incident malaria case with DHAP.

[figure not shown]

Figure 3 - Schematic showing control and intervention arms proposed at the health center catchment level. PCD, passive case detection; RFTAT, reactive focal test and treat; RFDA, reactive focal drug administration; AL, artemether-lumefantrine; DHAP, dihydroartemisinin-piperaquine.

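### The primary analysis is to adjust for net coverage and spraying measured only at the two-year endline, while no pre-randomisation malaria measure enters the model

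*Protocol*

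**What the plan says.** Section 2.8.1 (Primary Aim, Analysis) makes a mixed effects regression with a health-centre random intercept the primary method, and then says "Analyses will account for environmental factors, socio-economic status, housing construction, education level, and demographic measures of the population as well ITN coverage". The same sentence goes on to include indoor residual spraying. No earlier malaria measure is listed.

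Section 2.5 (Surveys) shows where most of these variables come from: "A modified malaria indicator survey (Appendix 4) will be administered at the endline". Its items include net ownership and use, spraying history, household structure, education and an asset index. Their purpose is stated: "The above information will be enable us to control for any differences between the selected health centre catchment areas".

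The timing is clear. Section 2.1 describes seropositivity as measured "through a random sample survey at the end (two years) of the intervention period", and the procedures for the primary aim run "1) randomization; 2) RFTAT with AL or RFDA with DHAP; 3) endline survey". No baseline survey appears in the study design, participant groups, consent table, personnel or timeline.

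Table 1 in section 2.1 does hold earlier data: "Proposed selected health centre catchment areas along with data from these facilities for the last year". It gives case counts for September 2013 to August 2014 and RFTAT positivity. Their stated use is site selection, namely "a mean monthly incident malaria case load of < 25 and a mean test positivity during ongoing RFTAT of at least 5" per cent. The allocation text reads "Selected health centres will be randomized to either control or intervention arms, with 8 health centers per arm" and mentions no stratification or restriction on these values.

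**The concern.** A covariate in the primary model of a randomised trial should be fixed before allocation, or at least be beyond the reach of the intervention. Net use and spraying over two years meet neither condition. Households and programmes may direct nets and spraying to places where malaria persists, and how much malaria persists is what the two arms are meant to change. Conditioning on such a variable can remove or distort part of the arm effect.

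There is a second cost. With 16 clusters there are only 16 - 2 = 14 between-cluster degrees of freedom. Each covariate entered at cluster level uses one, and any chance correlation with arm inflates the variance of the arm effect.

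Meanwhile the pre-randomisation catchment values, which could correct a chance imbalance in starting malaria without these risks, are not in the primary model.

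**Working it through.** **1. When each covariate is measured, and whether arm could affect it.**

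| Covariate in 2.8.1 | Source and time | Could arm or local malaria change it? |
|---|---|---|
| Net coverage, spraying | Endline survey (2.5) | Plausibly yes |
| Housing, education, wealth | Endline survey (2.5) | Unlikely; measured late |
| Environment | Not a survey item; remotely sensed data are planned under Secondary Aim 4 | No |
| Malaria before randomisation | Table 1 | No, but not in the model |

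The bias argument therefore rests on nets and spraying.

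**2. The plan's own figure.** The inputs from section 2.9 are control seropositivity p0 = 5%, between-cluster coefficient of variation k = 0.5, m = 500 children per cluster, c = 8 clusters per arm and 80% power. I assume two-sided alpha of 0.05. The formula for unmatched cluster trials is

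c = 1 + (1.960 + 0.842)² × [p0(1-p0)/m + p1(1-p1)/m + k²(p0² + p1²)] / (p0 - p1)².

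With p1 = 1.915%, the bracket is 0.0000950 + 0.0000376 + 0.0007167 = 0.0008492. Then 7.849 × 0.0008492 / 0.0009517 = 7.00, and adding 1 gives 8.00. The relative difference is 1 - 1.915/5 = 61.7%, the midpoint of Table 3. (The text above Table 3 says 64.5%. That mismatch is separate and nothing here depends on it.) About 84% of the bracket (0.0007167/0.0008492) is between-cluster variance, so the cluster-level part of the model is what matters.

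**3. Cost of cluster-level covariates unrelated to outcome.** I simulated random covariates for 16 clusters split 8 v 8. The interval ratio is the mean standard-error inflation times the ratio of t quantiles.

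- One covariate: 1.039 × (2.160/2.145) = 1.047, about 5% wider.
- Three covariates: 1.134 × (2.201/2.145) = 1.164, about 16-17% wider depending on the simulation run.

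Three is the relevant upper case, because environment, spraying and net coverage are the factors that vary mainly between catchments.

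**4. Effect of one pre-randomisation covariate, with its own cost charged.** Residual k = 0.5 × √(1 - r²), where r is the correlation between the baseline value and endline cluster seropositivity. The documents give no r, so a range is assumed. The charge multiplies the standard error by about 1.048, that is, the bracket by 1.048².

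| Assumed r | Residual k | Detectable difference, uncharged | Charged |
|---|---|---|---|
| 0 | 0.500 | 61.7% | about 64% |
| 0.3 | 0.477 | 59.7% | about 62% |
| 0.5 | 0.433 | 55.9% | about 58% |
| 0.7 | 0.357 | 49.4% | about 51% |

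The charged figure equals the unadjusted 61.7% at r of about 0.33.

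**5. Is chance imbalance realistic?** Across the 20 facilities in Table 1, positivity runs from 5.2% to 19.2% and yearly cases from 83 to 262. Drawing 16 of the 20 and splitting them 8 v 8 without restriction (20,000 draws), the larger arm mean exceeds the smaller by a median factor of 1.14 for positivity and 1.12 for cases. At the 90th percentile the factors are 1.30 and 1.32.

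**The case against.** The strongest reply is that the sentence in 2.8.1 is general. It does not fix the level at which each covariate enters, or whether an unadjusted estimate comes first, and the statistical analysis plan may settle both. That is fair for the exact covariate list and for the absence of a baseline term taken alone. But the protocol itself commits the analyses to account for net coverage and spraying, and 2.5 fixes when they are measured. That commitment is what needs changing.

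A reader might infer four stronger things that the documents do not support.

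- **That all the endline covariates bias the effect.** Housing, education and wealth are unlikely to respond to arm, and environmental factors can be remotely sensed.
- **That the interval must widen, perhaps by a third or more.** Widening of that size needs five or more purely cluster-level covariates with no relation to outcome. Household items entered at household or child level do not each use a between-cluster degree of freedom. Prognostic covariates can also pay for themselves: three cluster-level ones break even if they explain about 26% of between-cluster variance (1 - 1/1.164²).
- **That baseline adjustment will certainly improve precision.** Once charged for its own degree of freedom, it gives nothing at r = 0.3. The selection limits on case load and positivity also narrow the range of the baseline values, which makes a high r less likely.
- **That Table 1 is ready to use as a case rate.** It has no population denominators, it lists 20 proposed facilities rather than the 16 to be randomised, and its data end in August 2014, whereas section 1.5 looks ahead to a test available in 2017.

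Sections 2.5 and 2.11 contain remnants that mention more than one survey, but every operative section describes an endline survey only.

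**Conclusion.** The point holds in a limited form. As written, the primary effect is to be conditioned on two variables, net coverage and spraying, that are measured two years into the intervention and can respond to local malaria. That can bias the arm effect. A response to arm or case load is plausible but not documented, and neither the direction nor the size of any bias can be derived from the documents.

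For the other survey covariates the weakness is late measurement, plus about 5% (one) to 16-17% (three) on the interval for factors entered at cluster level, if they are unrelated to outcome.

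Replacing these with one baseline catchment value takes the detectable difference from 61.7% to about 62%, 58% or 51% at assumed correlations of 0.3, 0.5 and 0.7. The precision gain is real only if the baseline value is at least moderately prognostic. The firmer reasons for the change are that it avoids post-randomisation adjustment and can correct an imbalance of the size shown above.

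**What to change.** Rewrite the covariate sentence in 2.8.1 so that the primary model contains arm, age group and one pre-randomisation catchment value for the 16 randomised centres. Use RFTAT positivity or log case count, taken from Table 1 or, preferably, from the same routine data updated to just before randomisation. Do not specify a case rate unless denominators are added. Choose the variable before outcome data are seen.

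Move adjustment for endline nets and spraying, together with the other endline survey covariates, to a sensitivity analysis labelled as adjusting for post-randomisation measurements. Amend the closing sentence of 2.5 to match. The project summary also promises difference-in-differences for the primary outcome, although no baseline seropositivity is collected; reconcile that statement in the same edit.

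The cost is a wording change and one between-cluster degree of freedom (14 to 13). No new survey is needed. If the baseline value turns out unrelated to outcome, the detectable difference worsens from 61.7% to about 64%.
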